## Background

Death from opioid overdose is the leading cause of death among drug users, and has more than doubled in the US over the last 15 years [1, 2] in what is often characterized as an ‘overdose epidemic.’ A main mechanism is the development of addiction to opioid agonist drugs like heroin and/or illicit diversion of prescribed opioid medications [3]. A chronically relapsing disorder [4], addiction to illicit opioids often includes criminal activity, poly-drug use and blood-borne infections such as HIV [5].

Due to high risk of relapse and overdose associated with abstinence, the preferred treatment for opioid addiction is substitution of the illicit opioid with a prescribed opioid medication like the full opioid agonist methadone [6] or partial opioid agonist buprenorphine [5]. This agonist replacement therapy (ART) is generally effective at reducing illicit opioid use, overdose mortality [7], as well as important drug-related outcomes such as criminal activity [8] and injection-related disease [9].

As ART presents a risk of illicit diversion and abuse of prescribed methadone or buprenorphine [10], ART providers will often attempt to minimize this risk by utilizing control measures such as supervised medication intake, urine drug screens, limits on take-home dosing and–travel outside the catchment area [5, 11]. A disadvantage of these control measures is their tendency to reduce patients’ sense of personal freedom, potentially undermining their motivation to remain in ART [5]. As methadone, a full opioid agonist, is considered to have a high potential for abuse and overdose, the partial opioid agonist buprenorphine is sometimes preferred. The abuse risk of buprenorphine can be further reduced when combined with a component of the short-acting opioid antagonist naloxone; this combination product tends to not cause withdrawal when ingested correctly (sublingually), but is likely to cause some withdrawal symptoms if the medication is injected [12].

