#### Determination of sample size

In compliance with current recommendations for non-superiority trials [34], a minimum sample size has been estimated for two scenarios:

The superiority scenario assumes that XR-NTX participants will have opioid-negative samples on a mean of 7 out of the total 12 (7/12 or 0.58) samples, while participants receiving buprenorphine-naloxone will display a mean of 4 opioid-negative samples (4/12 or 0.33). With a 95 % significance level (*p* < 0.05) and a standard deviation of 3 in both medication groups, and power (beta) set to 90 %, a sample size of 17 patients/medication arm or *n* = 34 total is estimated to be sufficient for analysis. The estimated frequency of opioid use in each group is based on data from Norwegian patients receiving sustained release naltrexone [22] or on the frequency of illicit opioid use during buprenorphine maintenance in the Norwegian national ART program.

In the non-superiority scenario, using a beta of 90 %, we assume that both groups will retain 70 % of their participants at the end of Week 12 and set 20 % as the non-superiority margin; this yields a minimum sample size of *n* = 58 in each group/*n* = 116 total.

Based on the sample size calculations and the risk of dropout of a significant proportion of participants, we have set the recruitment target for *n* = 180 total, or *n* = 90 for each medication group. This will be facilitated by characteristics of design (few exclusion criteria, open-label allocation, outpatient data collection often coinciding with medication and counseling), prioritization of amount–and types of data collected. Information about the study will be distributed at clinical sites as well as outreach -, housing- and criminal justice facilities and the internet; these efforts are anticipated to attract the initial *n* = 30 patients whose presence in the larger community of opioid users will be sufficiently inform more potential participants to contact study staff for information.

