#### Analysis sets

In addition to analyses of data from all patients who complete the 12-Week study, Intention-to-treat (ITT) analyses of efficacy endpoints will be conducted with all patient data. Separate analyses sets may be conducted on different analysis sets depending on publication requirements: e.g. a modified intention to treat (MITT) set of randomized patients who receive at least one dose of their assigned medication and complete at least one study follow-up; or a per-protocol dataset of patients who exhibit compliance with medication–and attend all four outpatient follow-ups. Imputation will be conducted using the previous valid assessment (last observation carried forward) at the last attended study follow-up or (if no follow-up took place) from the inclusion dataset; imputation using data modeling may be considered pending satisfactory similarity to collected data. The inclusion dataset may be corrected for days spent in a controlled environment (e.g. on-site detoxification unit) in order to convey the most accurate picture of pre-study functioning. For analyses beyond the 84-day randomized period, imputation (e.g. ITT, MITT) will only be conducted if considered relevant to the research question.

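### Model-based imputation is conditional on resembling the collected data: an undefined, after-the-fact test that tends to fail a sound model when dropout is informative and returns the analysis to carry-forward

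*Protocol article*

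**What the plan says.** Under Analysis sets, the protocol states that "Intention-to-treat (ITT) analyses of efficacy endpoints will be conducted with all patient data". It then fixes the default for missing values: "Imputation will be conducted using the previous valid assessment (last observation carried forward) at the last attended study follow-up". A patient who attended no follow-up gets the value from inclusion. The same sentence ends with the alternative: "imputation using data modeling may be considered pending satisfactory similarity to collected data". The text does not say what is compared with what, by which measure, at what threshold, whether the comparison is made by arm, or whether it conditions on earlier visits.

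Missing data are expected. Under Determination of sample size, "we assume that both groups will retain 70 % of their participants at the end of Week 12", and the recruitment target is raised because of "the risk of dropout of a significant proportion of participants". Under Outcomes & instruments, intoxication is the example given of why a patient may be unable to complete a follow-up, so missingness may be tied to drug use. That passage also gives the primary outcomes priority at such visits, which reduces the loss but does not remove it.

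**The concern.** The sentence reads as an acceptance test: a model is admitted if its output looks like the data already in hand. That is not a criterion of validity. If patients who leave were doing worse at their last visits, a correct model under missing at random uses those histories and produces values unlike the observed Week 12 values. The departure from the observed data is the correction the model is there to make, and the stated condition counts it against the model.

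Two consequences follow. The method is chosen by looking at its own result. And when it is turned down, the analysis goes back to carry-forward, which assumes that nothing changes after the last attended visit. Self-reported abstinence, a primary outcome, is exposed. So are the other four-weekly measures, and the urine results if they are imputed.

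**Working it through.** No figure in the plan depends on this rule, so there is none to reproduce. The check is of the logic, with a simulation as illustration.

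**Step 1: the algebra.** Let d be the fraction missing at Week 12 and D the mean of leavers minus the mean of stayers. The full mean equals the stayers' mean plus d × D, so an analysis of observed cases alone has bias −d × D. A valid imputation must reproduce D. When D = 0 there is no selection bias to remove and imputed values look like observed ones. As D grows, the correction matters more and the resemblance falls.

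**Step 2: inputs from the document.** The target is 90 per group and Week 12 retention is 70%, both under Determination of sample size. So d = 1 − 0.70 = 0.30, or 0.30 × 90 = 27 leavers and 63 stayers. The 70% is treatment retention, so 30% missing data is a proxy.

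**Step 3: assumptions, none from the document.**
- One arm, 400 runs.
- Each visit equals 0.7 times the previous value plus noise with SD 0.7, so the SD is about 1.
- The mean shifts by −0.5 SD after the last attended visit.
- Higher values are read as more use.
- Dropout depends on the last observed value with logit slope 0 to 3.
- The model is a regression imputation on that value, 20 draws per run.
- Similarity passes if the median Kolmogorov–Smirnov p-value, imputed against observed, exceeds 0.05. Otherwise carry-forward is used.

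**Step 4: results (bias in SD).**

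| Dropout slope | Model accepted | Imputed minus observed | Observed cases only | Model, no condition | Carry-forward | With the condition |
|---|---|---|---|---|---|---|
| 0 | 99% | 0.00 | 0.00 | 0.00 | +0.15 | 0.00 |
| 0.5 | 88% | 0.33 | −0.10 | 0.00 | +0.18 | +0.02 |
| 1 | 34% | 0.59 | −0.18 | 0.00 | +0.21 | +0.14 |
| 2 | 3% | 0.86 | −0.26 | 0.00 | +0.23 | +0.22 |
| 3 | 0.5% | 0.98 | −0.29 | +0.01 | +0.24 | +0.24 |

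The table agrees with Step 1. At slope 1, −0.30 × 0.592 = −0.178, against −0.175 simulated. At slope 3, −0.30 × 0.984 = −0.295, against −0.287.

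**Step 5: what the sign depends on.** At slope 0 the carry-forward bias is 0.30 × 0.5 = 0.15, which comes wholly from the assumed −0.5 shift. With a shift of +0.5 it would be −0.15. The sign is therefore a product of the assumed trajectory.

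**Step 6: dropout that depends on the unseen Week 12 value.** At slopes 1 and 2 on that value, the model was accepted in 81% and 42% of runs. Bias was −0.14 and −0.22 for the model, +0.10 and +0.08 for carry-forward, and −0.09 and −0.05 with the condition. Here the model under missing at random is also biased. The condition comes out nearer zero because two errors of opposite sign partly cancel under the assumed shift. This does not support the condition. It shows why sensitivity analyses for departures from missing at random are needed.

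**The case against.** The wording is loose enough to bear a milder meaning. Collected data include leavers' own earlier visits, so a check of model fit, or a comparison conditional on earlier visits, would fit the words and would be defensible. That stands as a possibility, but the text does not say it. The condition also does not always reject: the assumed check still passed 88% of runs when imputed and observed means differed by 0.33 SD. So the claim is a tendency, not that the rule admits models only when leavers look like stayers.

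A reader might go further and infer that the rule gives leavers the stayers' values, pushes both arms' abstinence upward and hides a difference caused by unequal dropout. For instance, assume stayers abstinent on 60% of days and leavers on 30%. Dropout of 40% against 20% gives 0.6 × 60 + 0.4 × 30 = 48% and 0.8 × 60 + 0.2 × 30 = 54%, a gap of 0.06 × 84 = 5.0 days that would vanish if leavers were set to 60%. The documents do not support this. A rejected model is replaced by each leaver's own last value or inclusion value, not by stayers' values. The 60%, the 30% and the unequal split are all assumptions. With the plan's equal 70% retention, both arms come to 0.7 × 60 + 0.3 × 30 = 51% and there is no gap to hide. In the simulation the bias with the condition overstates use, which means abstinence is understated, and only one arm was simulated.

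Other features limit the reach. Modelling is optional. The urine option that counts negative tests received needs no imputation. Retention is analysed by Kaplan–Meier and log-rank. Under Statistical analyses, the statistician works with masked labels, and the main approach is a mixed model that can use all observed visits. These points stand as mitigation. Masking, however, does not make the criterion valid. The same section allows ANOVA or linear regression instead, and a mixed model fitted to carried-forward values would lose its advantage.

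Finally, the article is a condensed protocol, and the imputation model and its variables may properly sit in the analysis plan. Their absence is not the point here. The acceptance condition is stated in this document, and it is a poor one.

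**Conclusion.** The point holds in a limited form. The protocol makes carry-forward the default and ties the better-founded alternative to an undefined resemblance, judged after the data are seen. Read plainly, that makes a valid model less likely to be accepted the more informative the dropout is. The acceptance rates above illustrate the pattern and rest on the assumed check, slopes and trajectory. They are not forecasts for this trial.

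The direction and size of bias in the treatment comparison depend on patients' trajectories and on any difference in dropout between arms. The documents give neither, so no upward direction and no number of days should be claimed. If the intended check is conditional on earlier visits, one sentence saying so would remove much of the concern, though it should still not decide the method. The matter is worth correcting because primary abstinence outcomes are exposed and the change is cheap.

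**What to change.** Delete the closing condition of that sentence. Then, before unmasking:

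- Name one approach valid under missing at random as the main handling of missing abstinence data: the mixed model on all observed visits, or multiple imputation by arm using earlier urine results, self-report and retention day.
- Move last observation (and inclusion value) carried forward to a sensitivity analysis.
- Add delta-shifted analyses, in which missing values are made progressively worse, up to treating every missing day as non-abstinent.
- Keep imputed-versus-observed comparisons, conditional on earlier visits, as a diagnostic only and not as a rule for choosing the method.

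The cost is a change of wording, a standard imputation or mixed-model run, a little more analysis and possibly wider intervals.

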#### Dissemination of results

Scientific dissemination will occur under ICMJE guidelines for authorship and publication. Dissemination of results to a broader audience will be conducted via the University of Oslo's - and the research group’s websites, general news media in Norway and internationally.

## Discussion

This study has the potential to become the first comparison between extended-release naltrexone and daily buprenorphine-naloxone for opioid dependence. Such comparisons are currently lacking from the knowledge base [47]. In addition, longer-term data on the performance of XR-NTX in opioid dependent patients is central in evaluating the clinical feasibility of XR-NTX in this high-risk, chronically relapsing patient group. Registry linkage data provides an option to study the clinical trajectories of participants before, during and after the active follow-up phase, providing opportunities to address long-term recovery outcomes as well as concerns of increased overdose risk upon termination of naltrexone medication.

Parts of the original protocol have not been possible to implement: One site investigator has passed away prematurely without leaving a competent successor, leading to the premature closing of one site. A policy change greatly reduced the number of patients imprisoned for possession of minor quantities of drugs, meaning it has not been feasible to recruit a large proportion of participants from the criminal justice system. In order to maintain recruitment targets using only clinical sites, the inclusion phase of the study has had to be extended about by 25 % compared to the original schedule. As the clinical population of opioid users has a lower incidence of lethal overdose than opioid users discharged from criminal justice settings, overall mortality figures are expected to decrease below what is considered a meaningful basis for statistical estimation. Despite these implementation difficulties, we consider the protocol to retain its intended value as a ‘first of a kind’ comparison.
